## Abstract

**Background:**

Complete tooth loss is a significant global oral health issue, particularly impacting older individuals with lower socioeconomic status. Computer-assisted technologies enhance oral healthcare access by the elderly. Despite promising in vitro reports on digital denture materials, evidence from randomized clinical trials (RCTs) is lacking to verify their performance. This cross-over RCT will investigate whether 3D-printed implant-retained mandibular overdentures (IMO) are more satisfactory for edentulous seniors than those made through traditional methods.

**Methods/design:**

We will recruit 26 completely edentulous participants (any sex/gender) based on the following eligibility criteria: age ≥ 60 years, no tooth extraction in the past 12 months, two implants in the lower jaw, and need for new dentures in both jaws. Each participant will receive two denture pairs, either manufactured by 3D printing or traditionally, to be worn in a random order. A timeline of 3 months with each denture pair will be considered for outcome assessment (total: 6 months). Patient satisfaction with dentures will be measured by the McGill Denture Satisfaction Questionnaire. We will evaluate other patient-reported outcomes (including oral health-related quality of life) as well as clinician-assessed quality and cost. At the end of the trial, participants will choose which denture pair they wish to keep and interviewed about their experiences with the 3D-printed IMO. The quantitative and qualitative data will be incorporated through an explanatory mixed-methods strategy. A final quantitative assessment will happen after 12 months with the preferred IMO to assess the long-term performance and maintenance needs.

**Discussion:**

This mixed-methods RCT will explore patient experiences with 3D-printed IMOs, aiming to assess the potential for altering clinical practice and dental public health policies. Our results will inform policies by showing whether 3D printing offers comparable outcomes at lower costs, facilitating greater access to oral care for the elderly.

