### Objectives and hypothesis

We aim to conduct the first mixed-methods cross-over RCT to determine the efficacy and patients’ experience with 3D-printed implant-retained mandibular overdentures (IMO), compared to the traditional method, for independently living edentulous seniors who have two implants in the anterior mandible, as purported by the McGill Consensus on Implant Overdentures [26]. Our null hypothesis is that IMOs produced by computer-aided design and 3D printing are as satisfactory to edentulous seniors as those fabricated using traditional methods.

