
The cost-effectiveness of both methods will be compared by using overall patient satisfaction to measure the effect of interventions. Economic analysis will have the perspective of the public health system of Quebec. All expenditures and resources through all stages of dental care (from clinical exam to denture adjustments) will be included, considering a short-term/3-month time frame. Results will be expressed by the incremental cost-effectiveness ratio (ICER).5.Adverse effects: All adverse events during the RCT will be recorded at each post-delivery appointment and follow-up. Common events, i.e., mucosal injuries and difficulties with new dentures, will be rated on a three-point ordinal scale [50]. More uncommon (nausea, change in taste and lingering speech difficulties) and rare events (allergy to denture materials) will be reported on a binary scale.6.Choice of overdenture and patient experiences: A qualitative analysis will be carried out to better understand patients’ perception of CAD/CAM dentures and to find out any emergent themes besides (1) patients’ reasons for choosing a specific denture pair and (2) their experience of using a 3D-printed IMO. By adopting a descriptive approach, individual semi-structured interviews will be carried out to obtain an in-depth understanding of patients’ experiences and preferences [51].

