### Sample size estimation

The planned enrollment comprises 26 participants, based on overall patient satisfaction. A minimal important difference of 10 mm (10% of the VAS) was used for the estimation, as done in previous RCTs [41, 54]. A standard deviation of 7.5 mm was chosen for the difference in satisfaction [55]. Considering a 2-sided alpha of 0.01 to compensate for the number of secondary outcomes and a power of 90%, the RCT requires *n* = 21 for superiority hypothesis testing (i.e., the confidence interval for between-treatment differences would exclude zero) [56]. The final sample size is drawn from including further 20% to the planned *n* to compensate for possible dropouts; although withdrawals will unlikely pass 10% [41, 55, 57], additional participants may be lost due to aging-related issues (e.g., worsening of systemic diseases, and death).

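### The abstract promises a finding of comparable outcomes at lower cost, but the plan fixes only a superiority test and states no margin by which comparability could be judged

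*Protocol article*

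**What the plan says.** The Abstract (Discussion) says that policy will be informed by "showing whether 3D printing offers comparable outcomes at lower costs".

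The rest of the document sets up a different question. The Abstract (Background) asks whether 3D-printed overdentures "are more satisfactory for edentulous seniors than those made through traditional methods". Under Objectives and hypothesis, equality is the null: "Our null hypothesis is that IMOs produced by computer-aided design and 3D printing are as satisfactory to edentulous seniors" as those made traditionally. Sample size estimation gives n = 21 "for superiority hypothesis testing (i.e., the confidence interval for between-treatment differences would exclude zero"), with two-sided alpha 0.01 and 90% power. On the effect size it says: "A minimal important difference of 10 mm (10% of the VAS) was used for the estimation". On variability: "A standard deviation of 7.5 mm was chosen for the difference in satisfaction". Quantitative analysis plans GEE with 95% confidence intervals. No section states a non-inferiority or equivalence hypothesis, or a margin.

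For the economic analysis, Outcome measures takes overall satisfaction as the effect and says: "Results will be expressed by the incremental cost-effectiveness ratio (ICER"). The same section also plans total cost per fabrication method and a yearly cost difference.

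**The concern.** In a superiority test with equality as the null, comparable satisfaction is the null hypothesis, and failing to reject a null does not establish it. The plan uses 10 mm to size the trial but gives it no role in reading the result, because the stated criterion is only that the interval excludes zero. A result near zero would therefore have no agreed interpretation, and a margin chosen after the data are seen would carry little weight with the public programmes that the article's main Discussion addresses.

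The economic analysis has a related weakness. The denominator of the cost-effectiveness ratio is the satisfaction difference. If outcomes really are comparable, that denominator is near zero.

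**Working it through.** **Inputs from Sample size estimation.** Difference 10 mm; standard deviation (SD) of the difference 7.5 mm; two-sided alpha 0.01; power 90%; n = 21, raised by 20% to 26.

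**Reproducing n = 21.** For a paired comparison, n = [SD × (2.576 + 1.282) / 10]².
- With SD 7.5 this is 8.37, so 9. The exact paired t calculation gives 12.
- With SD 7.5 × √2 = 10.6, the paired t calculation gives 21, the plan's figure.
- 21 × 1.2 = 25.2, which rounds up to 26.

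Since 21 follows from 10.6 and not from 7.5 as written, both values are carried below.

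**Expected half-width of the interval**, t(n−1) × SD/√n. For example, 2.086 × 7.5/√21 = 3.41 mm.

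| SD of difference | n | 95% CI | 99% CI |
|---|---|---|---|
| 7.5 | 21 | 3.41 | 4.66 |
| 7.5 | 26 | 3.03 | 4.10 |
| 10.6 | 21 | 4.83 | 6.59 |
| 10.6 | 26 | 4.28 | 5.80 |

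All are below 10 mm, which has two consequences. An interval centred near zero would exclude a 10 mm difference either way. Conversely, at n = 21 an observed difference of about 3.4 to 6.6 mm would already exclude zero while lying below the plan's own minimal important difference.

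**Power to show comparability** (whole interval inside ± margin; true difference zero; paired t; 200,000 simulated trials). The documents give no comparability margin, so both margins are assumptions: 10 mm is the plan's minimal important difference and 5 mm is half of it.

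| SD | n | ±10 mm, 99% CI | ±10 mm, 95% CI | ±5 mm, 99% CI | ±5 mm, 95% CI |
|---|---|---|---|---|---|
| 7.5 | 21 | 99.7% | >99.9% | 24% | 66% |
| 7.5 | 26 | >99.9% | >99.9% | 46% | 81% |
| 10.6 | 21 | 83% | 97% | 1% | 14.5% |
| 10.6 | 26 | 94% | 99% | 3% | 29% |

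For one-sided non-inferiority at 10 mm with n = 21, power is 99.9% (SD 7.5) or 91.6% (SD 10.6) when the lower limit of a 99% interval is used, and over 99.9% or 98.4% with a 95% interval.

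Evaluable participants needed for 90% power to show comparability with a 99% interval: 14 (SD 7.5) or 24 (SD 10.6) at ±10 mm; 44 or 84 at ±5 mm.

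**Cost-effectiveness ratio when satisfaction is equal.** The documents give no cost difference, so −100 CAD is assumed and treated as known. With a true effect of zero, the standard error is 7.5/√21 = 1.64 mm. The ratio is −100 divided by a normal variable centred on zero, so its central 95% range is ±100/(0.0627 × 1.64), about ±970 CAD per mm, and its sign is positive in half of samples. Simulation gave −970 to +976. With SD 10.6 the standard error is 2.31 mm and the range about ±690. The range is proportional to the assumed cost difference: half the cost difference halves it, and five times the cost difference makes it five times as wide. The ambiguity of sign remains whatever the size of the cost difference.

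**The case against.** The strongest reply is that the stated objective, null hypothesis, test and sample size agree with one another: all are superiority. The mismatch comes from one sentence in the abstract, and the main Discussion speaks instead of better outcomes and of a superior or cost-effective treatment. Rewording that sentence would remove the conflict, and the primary test is untouched. This stands, and it is why rewording is offered as an alternative.

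It can also be said that an interpretation rule belongs in an analysis plan that is not shown. This carries less weight. The protocol article itself fixes the hypothesis framework and the success criterion, and both differ from the conclusion that its abstract announces.

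On costs, the ratio is not the only economic result. Total and yearly cost differences are planned separately, so lower cost can be shown without it. This too stands and makes the ratio a secondary matter.

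A reader might go further and infer that the trial cannot show comparability, that near-equality is the expected result, that a non-significant result will be reported as comparability, or that the cost conclusion will be uninterpretable. The documents support none of these. The planned intervals are narrow enough to exclude 10 mm. No section forecasts equal satisfaction or says how a null result will be worded. The ratio has no value only at a difference of exactly zero; near zero it is unstable.

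**Conclusion.** The point holds as a gap between the announced conclusion and the stated inference. Non-significance under this plan would not show comparable satisfaction, and no margin is given that would. What is missing is a decision rule; the sample size need not change if the margin is 10 mm. With that margin and a 99% interval, comparability power is 83% to 99.7% at 21 evaluable participants and 94% or more at 26.

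These figures assume a true difference of zero, a paired t analysis in place of the planned GEE, and an SD of the difference between 7.5 and 10.6 mm. A true difference away from zero would lower them. They also depend on 10 mm being accepted as a margin, which the plan does not argue. At 5 mm with a 99% interval, power would be at most about 46% at 26.

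This should be fixed, but it does not invalidate the superiority test. The instability of the cost-effectiveness ratio is real but lesser.

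**What to change.** Keep the superiority test and, before unblinding, add the following.

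- **Margin.** State and justify a comparability margin. The plan's own 10 mm is the natural candidate.
- **Confidence level.** Choose one, reconciling alpha 0.01 in Sample size estimation with the 95% intervals in Quantitative analysis.
- **Decision rule.** For 3D-printed minus conventional, conclude non-inferiority if the lower limit is above −10 mm, and comparability only if the whole interval lies within ±10 mm. State that comparability will not be inferred from non-significance.
- **Economic result.** Report the already planned cost difference with its confidence interval, and the incremental net benefit over a range of willingness-to-pay values (for example by paired bootstrap). Keep the cost-effectiveness ratio as a supplement.

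Alternatively, reword the Abstract (Discussion) to match the superiority aim and drop the claim of comparability.

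The cost is a paragraph of analysis text, some programming and the work of justifying the margin. With a 10 mm margin, no change to the planned 26 is required. Testing non-inferiority and then superiority on the same interval uses no extra alpha. A margin much tighter than 10 mm would require more participants.

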**Trial registration:**

ClinicalTrials.gov, NCT06155630, Registered on 04 December 2023. https://classic.clinicaltrials.gov/ct2/show/NCT06155630

**Supplementary Information:**

The online version contains supplementary material available at 10.1186/s13063-024-08097-7.

## Background

Complete tooth loss or edentulism remains one of the most burdensome oral health issues globally. Its prevalence is clustered in elderly populations and tends to remain high for many decades [1]. Edentulism can devastate well-being [2], with depressive symptoms worsening after complete tooth loss [3]. Poorer oral function after tooth loss, including impaired mastication [4], is closely linked to psychosocial discomfort and lower self-esteem [5, 6]. Moreover, edentulism has been shown to have likely systemic implications, as evidenced by its association with disability and earlier mortality in the elderly [7].

Even if implant-retained overdentures restore oral functionality and improve nutrition for the elderly [8–10], significant obstacles limit access to such care: (a) public funding for adult oral healthcare is limited, generally excluding prosthetic treatments for most without teeth [11, 12]; (b) high costs of private care, often not reimbursed, disproportionately affect those in lower socioeconomic groups, restricting their access to necessary dental services [13, 14]; (c) the need for multiple clinical visits, sometimes over six, poses challenges in terms of mobility and costs, particularly for those in long-term care or during health crises like pandemics [15, 16].

Computer-assisted technologies can greatly improve access to oral healthcare by the elderly. Fewer appointments for denture treatment, i.e., two to four, instead of five as with the conventional techniques, can reduce patient costs [17]. Patients can receive 3D images of their face with future dentures by internet, thus avoiding a clinical visit [18]. Moreover, digital files can be used to remake the same dentures in the absence of the patient, whereas analogic techniques need a repetition of the original workflow [19].

Among the computer-aided designed and manufactured (CAD/CAM) options for denture fabrication, 3D printing (or additive manufacturing) stands out as a highly promising technology. In comparison to traditional and other CAD/CAM workflows, 3D printed dentures have the potential to minimize material waste while achieving high speed and quality [20]. Even with promising in vitro reports of digital denture materials [21–24], however, evidence from randomized clinical trials (RCTs) is still missing to verify their clinical performance. Our recent scoping review (search update: March 1, 2023) [25] found no RCT on 3D-printed implant-retained mandibular overdentures (IMO), which have been considered the standard of care for complete edentulism by international consensuses [26, 27].

In addition, treatment success with dentures mostly depends on positive patient experiences. Integrating patient attitudes into the final dentures is vital for favorable results. Thus, patient-reported outcome measures (PROMs) are the core criteria in evaluating denture care, as for many healthcare interventions [23]. Yet, no study has explored patients’ experiences with the CAD/CAM dentures. In other words, it is unclear how patients perceive CAD/CAM dentures and whether they have a satisfactory performance from patients’ perspectives.

### Objectives and hypothesis

We aim to conduct the first mixed-methods cross-over RCT to determine the efficacy and patients’ experience with 3D-printed implant-retained mandibular overdentures (IMO), compared to the traditional method, for independently living edentulous seniors who have two implants in the anterior mandible, as purported by the McGill Consensus on Implant Overdentures [26]. Our null hypothesis is that IMOs produced by computer-aided design and 3D printing are as satisfactory to edentulous seniors as those fabricated using traditional methods.

## Methods

### Design and setting

This mixed-methods cross-over RCT will compare one experimental intervention (CAD/CAM dental prostheses) versus an active comparator (conventional denture fabrication methods). Outcome assessment will take place 3 months after each intervention, up to a total follow-up of 6 months. This will be a single-center RCT, conducted at the Faculty of Dental Medicine and Oral Health Sciences, McGill University (Montreal, Canada). The creation of this report adhered to the guidelines outlined in the Standard Protocol Items: Recommendations for Interventional Trials (SPIRIT) [28]. Figure 1 illustrates the standard protocol items diagram as suggested by SPIRIT, while the SPIRIT checklist for this study is provided in Additional file 1.

**Fig. 1 Fig1:**
[figure not shown]
The study protocol based on Standard Protocol Items: Recommendations for Interventional Trials (SPIRIT)

### Eligibility criteria

This trial will recruit edentulous patients seeking treatment with IMOs and maxillary complete dentures at McGill University.

The inclusion criteria is as follows: (i) elderly according to the age cut-off purported by the World Health Organization (age ≥ 60 years) [29] and living independently; (ii) completely edentulous; (iii) no tooth extraction within the past 12 months; (iv) two implants symmetrically distributed in the anterior mandible for three or more months before the trial interventions; (v) desire to receive both upper denture and lower IMO with new stud attachments; (vi) good understanding of spoken and written English or French; (vii) ability to provide written informed consent.

The exclusion criteria are as follows: (i) severe systemic disease or needing frequent hospitalization (i.e., American Society of Anesthesiologists Physical Status class > II) [30]; (ii) evidence of cognitive or motor impairment; (iii) acute or chronic symptoms of parafunctional or temporomandibular disorders; (iv) intraoral pathologies, either acute, progressive, potentially malignant, or capable to hamper denture fit; (v) signs of endosseous lesions or residual dental structures in panoramic radiographs; (vi) signs of implant failure, including clinical mobility, peri-implant radiolucency, unacceptable bone loss (0.2 mm/year after 1st year, or < 2 mm any time) and/or persistent signs/symptoms of pain, neuropathy, infection, and/or exudate [31].

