### Participant recruitment

We will recruit participants from the Greater Montreal area by verifying lists of prospective and past patients in our faculty. This will be done directly with the faculty’s clinical staff to reach those patients. Priority will be given to patients treated in recent years who may need to have their old IMOs replaced, e.g., 63 patients from 2010 to 2018 (around eight patients/year). Staff involved in clinical services will mention this study to patients and, if the latter have interest, refer them to our trial coordinator (TC). Patients without implants will be included if they comply with inclusion criteria #4 (two implants in the lower jaw) within the recruitment period.

Recruitment rate will be based on the ability of the researchers to provide treatment rather than participant availability, which is set at three patients/month. Recruiting 37% of the 63 patients available from 2010 to 2018 would reach the planned sample size (*n* = 26). Participants will be assigned to interventions with the recruitment flow, which will take nine months (from the 5th to the 14th month). Recruitment and care provision to participants will be spread over a 9-month period to reduce seasonal variation in their responses.

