### Outcome assessment timeline

Screening: The RA will invite potential participants, answer questions, and gather informed consent. The RA will complete a screening form checking eligibility criteria for all approached individuals. Panoramic radiographs will be requested, and recruitment will be conditional based on the results from the imaging (as in the exclusion criteria). As a piloting process, we collect data on gender conformity by two questionnaires, the Conformity to Feminine Norms Inventory-45 and Conformity to Masculine Norms Inventory-30 [52, 53].Baseline: Participants will return for baseline evaluation, *intraoral scanning*, and collection of sociodemographic information (including gender questionnaires) and medical and dental history (including patient experience with previous dentures). Participants will be asked to complete the MDSQ and OHIP-EDENT, and a dentist with experience in providing full dentures will apply the FAD instrument.Delivery and denture adjustments: Immediately after the end of the delivery appointments, the FAD instrument will be applied for each denture pair (same dentist as on baseline). The adverse effects form will be completed at the same time, as well as during each post-delivery appointment, scheduled or not.First follow-up (3 months): Participants will complete the outcome data questionnaires, the MDSQ and OHIP-EDENT. We will administer both questionnaires with a tablet computer away from the clinical setting. In turn, we will complete the FAD and adverse effects form, as described in the previous paragraph plus the colorimetric evaluation of denture bases.Second follow-up (6 months): Same as in previous time point (questionnaires and colorimetric analysis). At the end of the trial, participants will choose which overdenture they wish to keep. When faced with a choice, one is presented with the choices and the associated costs, which allows for a rationale decision. This is particularly important as dentures are typically not covered by the health care provider. Then, we will conduct individual semi-structured interviews about their experiences with the IMOs. The rich descriptive data obtained by qualitative interviews will help further explicate the quantitative findings. An experienced qualitative researcher will be responsible to conduct the interviews outside of the clinic using an interview guide with open-ended questions. Given the explanatory nature of this mixed-methods design, the interview guide will be created iteratively based on the quantitative outcomes which require further explanation. Each interview will be audio-recorded and transcribed verbatim.

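### One limb of exclusion criterion (vi) treats bone loss below 2 mm as unacceptable, which contradicts its own label

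*Protocol article*

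**What the plan says.** The Eligibility criteria section of the Protocol article requires two implants in the anterior mandible that have been in place for at least three months (inclusion criterion iv). It then excludes candidates whose implants appear to be failing: "vi) signs of implant failure, including clinical mobility, peri-implant radiolucency, unacceptable bone loss". A parenthesis says what makes bone loss unacceptable: "unacceptable bone loss (0.2 mm/year after 1st year, or < 2 mm any time". The same criterion continues with "and/or persistent signs/symptoms of pain, neuropathy, infection, and/or exudate" and cites a source for implant failure.

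Under Screening, the Outcome assessment timeline section has a form completed against the eligibility criteria for everyone approached. It requests panoramic radiographs and says "recruitment will be conditional based on the results from the imaging (as in the exclusion criteria".

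The Participant recruitment section gives priority to earlier patients who may need a replacement overdenture, for example "63 patients from 2010 to 2018 (around eight patients/year". It also lets in people who receive implants during the recruitment period. The Trial status section says recruitment has been open since January 2024.

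**The concern.** The parenthesis exists to define when bone loss is bad enough to exclude. Its second limb gives a less-than sign, so it defines small loss as the bad state. That conflicts with the word it is meant to explain and with the heading under which it sits. The first limb gives a rate with no comparison sign, so its direction has to be inferred.

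What is at stake is who enters the trial. If the limb were followed as printed, candidates with little bone loss would be turned away and this limb would not stop candidates with more. If it is not followed as printed, the rule in use differs from the published one, and a reader cannot tell from this document what the rule in use is.

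**Working it through.** No sample-size, power or alpha figure depends on this point, and the plan gives no derived figure to reproduce. The check is a literal reading of the criterion, with simple arithmetic on how its two limbs interact.

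**Inputs, all from Eligibility criteria, exclusion (vi)**
- Role: an exclusion, so meeting it removes the candidate.
- Limb A: 0.2 mm per year after the first year, with no sign.
- Limb B: less than 2 mm at any time.
- Connector: or, so meeting either limb is enough.

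**Step 1. Is the sign likely to be a text-extraction fault?** The same section has two other comparison signs, the age cut-off (≥ 60 years) and the physical-status class (> II). Both point the expected way. No other section restates the bone-loss limit, so nothing elsewhere corrects it.

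**Step 2. Limb B alone, read literally** (illustrative losses)

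| Total loss (mm) | Less than 2 mm? | Excluded by limb B? |
|---|---|---|
| 0.5 | yes | yes |
| 1.0 | yes | yes |
| 1.9 | yes | yes |
| 2.0 | no | no |
| 3.0 | no | no |
| 4.0 | no | no |

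The order is the reverse of what the label implies.

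**Step 3. Does limb A repair it?** Read limb A as an upper limit, which is the natural reading after the word unacceptable. The values below are assumed, for illustration only. Total = first-year loss + annual rate × later years.

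- Slow loss: 1.5 + 0.15 × 10 = 3.0 mm. The rate of 0.15 is below 0.2, so limb A is not met. The total of 3.0 is not below 2, so limb B is not met. The candidate is not excluded on bone loss.
- Faster loss: 1.5 + 0.25 × 10 = 4.0 mm. The rate of 0.25 is above 0.2, so limb A excludes, whatever limb B says.
- Small loss: 0.5 mm in total. Limb B is met, so the candidate is excluded whatever the rate.

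Limb A therefore catches some candidates with larger loss but not all. It cannot rescue those with small loss, because the limbs are joined by or.

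**Step 4. Implants less than one year old.** Limb A applies only after the first year. Inclusion (iv) accepts implants from three months, and Participant recruitment admits people implanted during the recruitment period. For them, limb B is the only numerical bone-loss rule.

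**Step 5. Where the rule is used.** Screening refers back to the exclusion criteria and ties recruitment to imaging. Panoramic radiographs are named only in exclusion (v), not in (vi). Criterion (vi) does list peri-implant radiolucency, which is a radiographic sign, so imaging plausibly informs it too. That link is a reasonable inference, not something the article states.

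**Step 6. Size.** The article gives no distribution of bone loss among the 63 past patients, so the number affected cannot be calculated.

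**The case against.** The strongest reply is that this is a one-character slip whose intended direction is clear from its setting. Taken literally, the limb would shut out people with healthy implants from a trial that requires implants and recruits former implant patients. Experienced clinicians are unlikely to follow it. The article also condenses a fuller protocol, and the screening form is not shown, so an error here does not prove an error there. All of this stands. It lowers the likelihood of wrong decisions but does not make the printed criterion usable. This is a stated error in the article, not a detail left to another document.

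The reply also rightly blocks several stronger readings that a reader might infer:

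- *Criterion (vi) as a whole admits everyone with larger loss.* It does not. The annual rate, mobility, radiolucency, pain, neuropathy, infection or exudate can each still exclude.
- *The annual limit is meaningless without a sign.* As a bare limit after the word unacceptable, it is naturally read as a maximum. Stating the direction is tidying, not a second error.
- *The slip endangers participants, raises dropout or adds noise to the primary outcome.* Nothing in the article supports this. The section on risks describes minimal safety risk. The Sample size estimation section already adds 20% for dropout and expects withdrawals unlikely to exceed 10%. Each participant wears both denture pairs on the same implants, with the same type of abutment and matrix, so implant condition at entry is largely shared by the two periods of the within-person comparison.
- *People have been wrongly screened since January 2024.* This is possible only if the form repeats the sign and staff followed it, and neither is shown.

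**Conclusion.** The point holds for one limb of one criterion. The bone-loss limit expressed as less than 2 mm contradicts both the word it defines and the heading it falls under, and nothing in the article resolves the conflict. Read literally, that limb excludes candidates with less than 2 mm of loss and does not exclude those with more, although other parts of the criterion may still exclude some of the latter.

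The conclusion rests on the printed sign being the authors' own, which the correct signs elsewhere in the section support. It does not rest on anyone having applied the sign literally. No effect on sample size, power or the treatment contrast is shown. The matter is still worth settling promptly, because the criterion decides who enters a trial that is already recruiting.

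**What to change.** 1. Reconcile the inequality in exclusion (vi) with the label, with the heading of the criterion and with the implant-failure source it cites. The investigators must confirm the threshold; this review proposes none.
2. State the annual limit with an explicit direction.
3. Check whether the full protocol and the screening form carry the same sign.
4. If the form does, correct it and re-check the screening decisions made since January 2024, covering both candidates turned away and candidates enrolled on the bone-loss item. If it does not, record that the error is confined to the article.

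The cost is a one-line correction and a check of one form. Only if the form is wrong does it extend to a review of the screening forms completed so far. The design, sample size and analysis need no change.
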